### **8.2.1 Suspected unexpected serious adverse reactions (SUSAR)**

Adverse reactions are all untoward and unintended responses to an investigational product related to any dose administered.

Unexpected adverse reactions are adverse reactions, of which the nature, or severity, is not consistent with the applicable product information (e.g. Investigator's Brochure for an unapproved IMP or Summary of Product Characteristics (SPC) for an authorised medicinal product).

The sponsor will report expedited the following SUSARs through the web portal *ToetsingOnline* to the METC:

- SUSARs that have arisen in the clinical trial that was assessed by the METC;
- SUSARs that have arisen in other clinical trials of the same sponsor and with the same medicinal product, and that could have consequences for the safety of the subjects involved in the clinical trial that was assessed by the METC.

The remaining SUSARs are recorded in an overview list (line-listing) that will be submitted once every half year to the METC. This line-listing provides an overview

of all SUSARs from the study medicine, accompanied by a brief report highlighting the main points of concern.

The expedited reporting of SUSARs through the web portal ToetsingOnline is sufficient as notification to the competent authority.

The sponsor will report expedited all SUSARs to the competent authorities in other Member States, according to the requirements of the Member States.

The expedited reporting will occur not later than 15 days after the sponsor has first knowledge of the adverse reactions. For fatal or life threatening cases the term will be maximal 7 days for a preliminary report with another 8 days for completion of the report.

#### **8.2.2 Annual safety report**

Not applicable

### **8.3 Follow-up of adverse events**

All adverse events will be followed until they have abated, or until a stable situation has been reached. Depending on the event, follow up may require additional tests or medical procedures as indicated, and/or referral to the general physician or a medical specialist.

### **8.4 Data Safety Monitoring Board (DSMB)**

Not applicable.

## 9. STATISTICAL ANALYSIS

### 9.1 Descriptive statistics

Baseline comparability of the groups will be shown by descriptive statistics and frequency tables (e.g. with information as gender, age, day care attendance etc).

Little is known about cellular immune responses against *Streptococcus pneumonia* quantitative endpoints of this study.

Frequencies of pneumococcal specific B cell populations (number of cells per  $10^6$  PBMC) and antibody concentrations (U/ml) will be calculated per patient.

B cell frequencies will be shown in medians and will be compared using non-parametric Mann-Whitney test. Results of antibody levels are expressed in geometric mean concentration (GMC) with 95% confidence interval (95% CI). Statistical differences in IgG GMC values will be assessed by log transformed unpaired t test. Correlations between IgG levels and circulating B cells will be assessed by Spearman correlation. All reported p-values are 2-sided, p-values smaller than 0.05 are considered significant. Analyses will be performed with SPSS 15.0 and PRISM4.

Other more qualitative endpoints, such as avidity and opsonophagocytoses, will be described as such.

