As of March 2011 all newborns will receive PCV10 vaccinations instead of PCV7.

[figure not shown]

Figure 1 Serotypes present in the three pneumococcal conjugate vaccines

When comparing pneumococcal vaccines an IgG antibody concentration of  $\geq 0.35$  ug/ml is used according to the recommendations of the WHO expert committee on biological standardization (4). The antibody concentrations are generally measured at one month after the complete series.

PCV13 showed to be non-inferior to PCV7 for 6 out of 7 serotypes present in PCV7 (except for 6B), when comparing proportions of responders ( $\geq 0.35$  ug/ml) and geometric mean concentrations (see SPC of PCV13 and (5)). In addition it was shown that PCV13 elicits OPA responses comparable to those elicited by PCV7.

PCV10 induces slightly lower antibody concentrations than PCV7 but are similar in terms of % responders (see SPC of PCV10 and (6)).

PCVs are thought to induce immediate protection through stimulation of antibody production by polysaccharide specific plasma B cells, sustained protection is conferred by a memory B cell pool which induces an accelerated increase in antibody concentrations during secondary immune responses seen after re-infection or boosting. Both the induction and maintenance of functional serum antibody concentrations have a cellular basis which is still poorly understood.

In general, antigens trigger naïve B-cells to expand and differentiate into two types of affinity matured B-cells: antibody secreting plasma B cells and memory B-cells. This immunological B cell priming occurs in highly organized structures of lymphoid tissues, under the influence of cognate CD4+ T cell help. Since plasma cells are unlikely to persist for more than 6-8 weeks (7) maintenance of steady state antibody levels over periods of years requires a continuous low level of differentiation of memory B cells into plasma cells. Factors such as recurrent antigen exposure for example through carriage might be involved in this process.

Carriage of the 7 serotypes present in PCV7 has decreased since the introduction of PCV in the NIP. This can influence the induction of memory and plasma B-cells, since there is hardly any natural boosting. Some of the extra serotypes present in PCV10 and PCV13 are still influenced by the natural boosters.

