**General aim of our pneumococcal projects is to determine the most optimal pneumococcal vaccination program for the NIP**

The number of vaccinations (2+1 versus 3+1), timing of vaccinations and the product choice depend on several factors such as;

- Humoral immunity, which is determined by the measurement of antibody response
  - Protection in the period of peak incidence of IPD (~8 months of age)
  - Protection after the booster
  - Kinetics of antibody concentrations over time
  - Percentage of antibody concentrations above the correlate of protection threshold
- Cellular immunity, which is determined by the measurement of plasma and memory B-cells, opsonophagocytoses and avidity
  - The vaccination schedule should lead to a sustained protection
  - Decrease in carriage (natural boosting) might lead to lower memory responses
  - Different conjugates can lead to differences in memory responses
    - PCV13 is an extended version of the PCV7 vaccine, 6 serotypes are added and both vaccines are conjugated to CRM197 carrier protein
    - PCV10 has a different conjugate, protein D of non-typeable *Haemophilus influenzae*
- Vaccine composition
  - Coverage of the products, especially in the Dutch population; PCV13 confers protection to more serotypes than PCV10

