### **Cellular immunity**

The aim of **our previous study** (KOKKI, cellular immunogenicity after PCV7 vaccination (NL24329.000.08), 2009) was to determine the development of the cellular immune response (plasma B cells and memory B-cells) for the 3+1 vaccination schedule of PCV7. Since 2009 several factors have changed:

- PCV10 has been introduced in the NIP (instead of PCV7)
- PCV13 was registered and might become part of the NIP in the future

- Carriage of the serotypes present in PCV7 have decreased in the five years following introduction of PCV7 in the NIP (2006), leading to loss of natural booster, and possibly lower memory responses

We lack information on the memory response to PCV10 and PCV13, therefore **our current study** aims to determine the development of the cellular immune response (plasma B cells and memory B-cells) for the 3+1 vaccination schedule of PCV10 and PCV13 immediately before and 7-9 days after the booster at 11-months of age. Time points of blood collection are similar to those in the previous KOKKI study. Also the antibody concentrations, avidity and opsonophagocytoses will be determined at these time points. These vaccines differ in number of serotypes and type of conjugate and could therefore differ in their cellular immunity.

A selection of 5-6 serotypes will be made; two of the four serotypes tested in the KOKKI study and three to four serotypes added by PCV10 and PCV13 for the current study. Selection will depend on serotype circulation just before analyses.

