## 2. OBJECTIVES

Primary: To compare immunogenicity (humoral and cellular) induced by PCV10 and PCV13 after the booster dose of a complete vaccination series (3+1, the current NIP schedule)

Secondary:

To compare immunogenicity (humoral) induced by PCV10 and PCV13 at 5, 8, 11 and 12 months of a complete vaccination series (3+1, the current NIP schedule)

To investigate the possible influence of the pneumococcal vaccination on the serological responses of other vaccine components of the NIP which are administered simultaneously in the other limb (DTaP-Hib)

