#### 7.1.2 Secondary study parameters/endpoints

##### *Pneumococcal serotypes*

- Opsonophagocytoses immediately before and 7-9 days after the booster at 11-months of age
- Avidity at 5, 8, immediately before and 7-9 days after the booster at 11-months and at 12 months of age
- Antibody concentrations and geometric mean concentrations (GMT) at 5, 8, immediately before and 7-9 days after the booster at 11-months and at 12 months of age
- Kinetics of antibody concentrations and geometric mean concentrations (GMT) over time (at 5, 8, 11 and 12 months of age)

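### Avidity and opsonophagocytosis are called qualitative and only described, so these secondary endpoints have no planned inferential PCV10-PCV13 comparison

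*Protocol*

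**What the plan says.** Section 7.1.2 lists both as secondary endpoints with set sampling times: "Opsonophagocytoses immediately before and 7-9 days after the booster at 11-months of age" and "Avidity at 5, 8, immediately before and 7-9 days after the booster at 11-months and at 12 months of age".

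Section 1 gives them a role in the comparison. Its list of factors for choosing a vaccination programme reads "Cellular immunity, which is determined by the measurement of plasma and memory B-cells, opsonophagocytoses and avidity", and its description of the current study adds, for the times just before and 7-9 days after the booster, "Also the antibody concentrations, avidity and opsonophagocytoses will be determined at these time points". Section 2 states the main objective: "Primary: To compare immunogenicity (humoral and cellular) induced by PCV10 and PCV13 after the booster dose of a complete vaccination series".

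The only analysis text that names either endpoint is in Section 9.1: "Other more qualitative endpoints, such as avidity and opsonophagocytoses, will be described as such". Earlier in the same section, "B cell frequencies will be shown in medians and will be compared using non-parametric Mann-Whitney test", and IgG is given geometric means with 95% confidence intervals and a t test on log values.

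**The concern.** The protocol does not merely leave the analysis of these endpoints open. It classifies them as qualitative and assigns description. A statistical analysis plan that followed the protocol would carry that choice forward, and one that did not would depart from it.

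The choice does not fit the protocol's own purpose. The rationale is that the two vaccines differ in carrier protein and may therefore differ in more than IgG concentration. Antibody quantity and antibody function need not move together. If the functional readouts are only described, the report can show what was seen in each group, but it will not say how large the difference between vaccines is or how uncertain that difference is.

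**Working it through.** **Step 1. The passages side by side.**

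| Endpoint | Status (Section 7.1) | Counted as immunity to be compared (Sections 1 and 2) | Analysis in Section 9.1 |
|---|---|---|---|
| Plasma and memory B cells | main | yes, cellular | medians, Mann-Whitney test |
| IgG | main at 12 months; secondary at other times | yes, humoral | geometric means with 95% CI, t test on logs |
| Opsonophagocytosis | secondary | yes, listed under cellular | description |
| Avidity | secondary | yes, listed under cellular | description |

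Lack of a power basis does not explain the difference. Section 4.4 says that no power calculation was possible for memory B cells, yet they receive a test.

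**Step 2. Which contrasts the sampling allows (Table 1).**

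- Before the booster: 1a and 2a give 8 ml; 2b gives a heel or finger stick; 1b gives no sample.
- 7-9 days after the booster: 1b and 2b.
- 12 months: all four sub groups.
- 5 and 8 months: group 2 only. Avidity at these ages has no concurrent PCV13 comparator in this study.

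**Step 3. The protocol's own figures (Section 4.4).**

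- IgG: variance 0.27 on the log10 scale, so SD = √0.27 = 0.52. With a 2-fold difference (log10 2 = 0.301), two-sided 0.05 and 80% power, n = 2 × (1.960 + 0.842)² × 0.27 / 0.301² = 46.8, so 47 per group. Then 47 / 0.80 = 58.75, so 59. Both stated figures reproduce.
- Cellular part: 33 × 0.90 × 0.85 = 25.2, so 25 evaluable per sub group. This also reproduces.

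None of these figures was derived for opsonophagocytosis or avidity.

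**Step 4. Illustrative precision.** The SDs are assumed, because the protocol gives none for either endpoint. The value 0.52 is borrowed from IgG (serotype 6B).

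- Half-width of the 95% CI on the log10 scale, 25 v 25: t(0.975, 48) × SD × √(2/25) = 2.011 × 0.2828 × SD = 0.569 × SD.
- Difference detectable with 80% power: (1.960 + 0.842) × 0.2828 × SD = 0.79 × SD.

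| Assumed log10 SD | 95% CI: estimate divided and multiplied by | Ratio detectable, 80% power |
|---|---|---|
| 0.40 | 10^0.227 = 1.69 | 10^0.317 = 2.1 |
| 0.52 | 10^0.296 = 1.98 | 10^0.412 = 2.6 |
| 0.80 | 10^0.455 = 2.85 | 10^0.634 = 4.3 |

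Power for a 2-fold ratio at SD 0.52: 0.301 / (0.52 × 0.2828) − 1.960 = 0.09, which is about 54%.

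**Step 5. Sensitivity to n.** The 15% loss behind the figure of 25 is failure to obtain enough blood cells. If these assays use serum and that loss does not apply, n is 33 × 0.90 = 29.7, about 30. At 30 v 30 and SD 0.52 the CI factor is 10^(2.002 × 0.52 × √(2/30)) = 10^0.269 = 1.86. The picture does not change.

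**The case against.** The strongest case for the current text has five parts.

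- **Description by group is still a comparison.** This stands. A reader might infer that the trial yields no PCV10-PCV13 information on antibody function. The protocol does not support that, since both readouts are planned for both vaccines around the booster. What is missing is the planned inference.
- **Section 9.2 may cover them.** Its last lines name a chi-square test for proportions and a t test or distribution-free method for means or medians. They name no endpoint and follow text on antibody concentrations only, whereas the sentence in Section 9.1 is specific. They do not clearly override it.
- **The protocol gives no assay, scale or detection limit for either readout.** Section 7.3 describes the IgG and ELISPOT methods only. This stands, and it is why the fix must depend on the scale and cannot prescribe a log-scale ratio for both. Nor does the remark in Section 1 that "it was shown that PCV13 elicits OPA responses comparable to those elicited by PCV7" settle the matter: it shows that such responses have been set side by side between vaccines, not that they were formally tested.
- **Describing secondary endpoints without a power basis is defensible.** This is fair as far as tests go, and an estimate with an interval needs no power claim. It asks for more than Section 9.1 states for B cells, which get a test but no interval.
- **An estimate with an interval may suggest more rigour than the design has.** Section 3 says children are randomised within each vaccine group, not between them. The estimates must be labelled accordingly.

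**Conclusion.** The point holds in a limited form. Section 9.1 makes a definite choice to treat two secondary endpoints as qualitative and to describe them, and this sits badly with Sections 1 and 2, which place them within the immunity to be compared. The consequence is the absence of a planned between-vaccine estimate with its uncertainty.

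Two further inferences are tempting and should not be drawn. First, the main comparison is not undermined: Section 7.1.1 rests it on B cells and IgG, and both keep their tests. Second, the CI factors of about 1.7 to 2.9 do not mean that a 2- to 3-fold difference could be reliably shown or excluded. At SD 0.52 the power for 2-fold is about 54%, and 80% power needs about 2.6-fold; at SD 0.8 it needs about 4.3-fold.

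All of these figures rest on an assumed SD, a log scale and 25 evaluable children per sub group. Section 11.1 foresees prioritising serotypes when little blood is available, so some serotypes may have fewer.

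**What to change.** Replace the sentence in Section 9.1 with text to this effect:

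> Opsonophagocytosis and avidity will be reported on the stated scale of each assay. For each serotype tested, PCV10 and PCV13 will be compared by an estimate with 95% CI: a ratio of geometric means for a titre; a difference or ratio of means or medians for an index; a difference in proportions if the result is only positive or negative. These estimates are supportive, and the vaccine groups were not randomised against each other.

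Name the contrasts:

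- Opsonophagocytosis: 1a v 2a before the booster; 1b v 2b 7-9 days after it.
- Avidity: 1a v all available group 2 samples before the booster; 1b v 2b after it; group 1 v group 2 at 12 months.
- Avidity at 5 and 8 months: descriptive within this study, because group 1 has no samples at those ages.

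Also state the scale of each readout and how values below any detection limit are handled.

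The cost is a few lines of text and some output on measurements already planned, with no new visit or sample. The downside is a larger number of secondary comparisons to report and to interpret with restraint.

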### 9.2 Univariate analysis

For group 2 of the currents study and the PCV13 group of the PIM study (vaccination at 2, 3, 4 and 11 months of age), differences in serotype specific antibody concentrations between different schedules will be analyzed. Primary, the antibody concentrations against pneumococcal polysaccharides for each serotype at 12 months in the different study arms will be calculated. GMCs and the degree of protection (the proportion with concentration  $> 0.35$   $\mu\text{g/ml}$ ) will be determined.

Secondary, the pneumococcal antibody concentrations at 5, 8, immediately before and 7-9 days after the 11-months booster and at 12 months of age will be calculated. For these endpoints, GMCs and the degree of protection (the proportion with concentration  $> 0.35$   $\mu\text{g/ml}$ ) will be determined. The antibody concentrations of the longitudinal samples of each child will be used to assess the kinetics.

Also the DTaP-Hib antibody concentrations at 5, 8, immediately before and 7-9 days after the 11-months booster and at 12 months of age will be calculated.

A chi-square test will be used to determine differences in proportions. A T-test or a distribution free variable will be used to test differences in mean or median.

### **9.3 Multivariate analysis**

Modifying factors, like family structure etc. will be analyzed for exploratory reasons only, in a multivariate regression analyses with as primary outcome measure antibody concentrations against the 13 serotypes *S. pneumoniae*.

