### 3. STUDY DESIGN

Children eligible to receiving the regular vaccinations of the NIP, born after August 2011 (assuring that all children are eligible for and will receive Hepatitis B vaccination)

A controlled, randomized, intervention trial with 2 groups (see figure 2 and table 1).

- Children of group 1 will be invited first (around the age of 1 month), since they have to receive all DTaP-IPV-Hib-HepB and PCV13 vaccinations as part of the trial
  - Vaccinations will be given during home visits
  - Children will be randomized over 2 sub groups in order to diminish the burden of the 8 ml blood sample (which is collected just before or 7-9 days after the 11-months vaccination)
  - For the immune memory, collect 33 children per sub group in order to have 25 evaluable children per sub group (sub group 1a and 1b)
  
- Children of group 2 will be invited around the age of 3.5 months, as to include them in the trial at the age of 5 months
  - Vaccinations are not part of the trial, since they already receive them during well-baby clinic visits
  - Children will be randomized over 2 sub groups in order to diminish the burden of the 8 ml blood sample (which is collected just before or 7-9 days after the 11-months vaccination)
  - For the immune memory, collect 33 children per sub group in order to have 25 evaluable children per sub group (sub group 2a and 2b)

Randomization will be done within group 1 and separately within group 2.

The randomization will not be done for the total study (group 1 and 2 together) since children of the PCV10 group already receive all proper vaccinations in the NIP and randomization would result in a long period between invitation at 1 month of age and inclusion at 5 months of age for the PCV10 group.

Figure 2 Study schedule

[figure not shown]

Blood samples (8 ml) are used for cellular immunogenicity (and 100 ul, of these samples will be used for humoral immunogenicity). Blood samples (100 ul) are used for humoral immunogenicity.

|                                                                                                                               | Group
1a
(PCV13) | Group
1b
(PCV13) | Group
2a
(PCV10) | Group
2b
(PCV10) |
|-------------------------------------------------------------------------------------------------------------------------------|------------------------|------------------------|------------------------|------------------------|

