The antibody concentrations will be compared for each of the serotypes included in the vaccine. Adjustment for multiple testing is not necessary for these comparisons because the serotypes will not be compared to each other and we are not interested in the overall null hypothesis of no effect (10).

**Antibody concentrations** will also be compared between the PCV13 group of the current study and the PIM study at 12 months after vaccination to bridge the two studies. Using the same sample size calculation as above, we need 59 children in this group as well.

Based on previous experience we expect a participation rate of 5% for all groups.

The study burden for group 1 involves only one 8 ml blood collection, vaccinations and one heel/finger stick (100 ul) Vaccinations are given at home, which parents appreciate. Since PCV13 is a registered vaccine and is not expected to give more side effects as PCV10, we assume that the study burden is perceived as relatively low, especially when the additional protection of three serotypes is taken into consideration.

The study burden for group 2 involves an 8 ml blood collection and 3-4 heel/finger sticks samples. Although the participants have no benefit in this trial, we expect that the heel/finger stick samples will not be perceived as a high burden.

Due to the lack of benefit for the children in group 2, recruitment rates after the first mailings amounted to around 2% instead of 5%.

In order to reach enough inclusions we need to invite approximately 1200 children for group 1 and 3500 children for group 2. We plan to enroll the children of group 1 in one month and the children of group 2 in 3.5 months.

The RCP region Noord Holland - Utrecht will be used and we will assess the exact region based on data from the Dutch Central Bureau for the Statistics (<http://www.cbs.nl>), in the same period of 2010. Due to a hampering recruitment for group 2, the RCP region Noord-Holland-Utrecht recruitment area will be extended with parts of Gelderland and Flevoland.

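### Vaccine is not randomised in any PCV10-PCV13 comparison, yet the planned tests are unadjusted and the recorded covariates are kept for exploratory use

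*Protocol*

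**What the plan says.** Protocol Section 3 describes "A controlled, randomized, intervention trial with 2 groups". The same section then says: "Randomization will be done within group 1 and separately within group 2". It gives the reason: the PCV10 children already receive their vaccine through the national programme, and joint randomisation would leave a long gap between invitation and inclusion. Section 7.2 confirms that the envelopes assign only the sub group, that is, the timing of the 8 ml sample.

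The primary objective (Section 2) compares PCV10 with PCV13 after the booster, through two contrasts:

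- **IgG at 12 months.** Sections 1 (Humoral immunity), 4.4 and 9.2 compare group 2 with the PCV13 arm of PIM that had the same 2, 3, 4 and 11 month schedule. Group 1 serves as a bridge to PIM.
- **B cells before and after the booster.** PIM is described as a humoral study, so this contrast is group 1 against group 2.

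For the analysis, Section 9.1 states: "Statistical differences in IgG GMC values will be assessed by log transformed unpaired t test". B-cell frequencies get a Mann-Whitney test, and baseline comparability is described only. Section 9.2 adds a chi-square test and a t-test or distribution-free test. Section 7.1.3 lists the recorded covariates, among them day care, family members, breast feeding, sex, birth weight and gestation. Section 9.3 says that modifying factors "will be analyzed for exploratory reasons only, in a multivariate regression analyses". No other adjusted analysis appears.

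**The concern.** An unadjusted two-sample test is a fair test of vaccine when chance decides who gets which vaccine. Here it does not. Any difference in exposure, age at sampling, region or type of family that also affects the immune response is counted as a vaccine effect, and the p-value takes no account of it. The bias can create a difference or hide one.

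The protocol gives a reason to take this seriously for some serotypes. Section 1 expects those added to PCV7 still to be under natural boosting, which depends on exposure to carriers. The results are meant to inform the Health Council on vaccination strategy.

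This is not a gap that a statistical analysis plan could simply fill. The protocol names the unadjusted tests and fixes the covariate regression as exploratory, so a plan that gave covariates a main role would depart from it.

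**Working it through.** **1. How groups 1 and 2 come about**

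| | Group 1 (PCV13) | Group 2 (PCV10) | Source |
|---|---|---|---|
| Invitation | about 1 month old, about September 2011 | about 3.5 months old, about January 2012 | Section 3, Table 1 |
| Entry condition | 2 months old, unvaccinated | 4-6 months old, three doses completed | 4.2 |
| Vaccination | at home, by the study team | well-baby clinic | Summary, 5.1 |
| Region | Noord-Holland, Utrecht | the same, but the "recruitment area will be extended with parts of Gelderland and Flevoland" | 4.4, 7.3 |
| Uptake | 5% expected; 66/1200 = 5.5% planned | about 2% seen; 66/3500 = 1.9% planned | 4.4 |
| Enrolment | 1 month | 3.5 months | 4.4 |

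These differences bear on the cellular primary outcome. For the IgG contrast with PIM (2010-2012), study and calendar period are further differences, and the protocol does not describe how PIM recruited.

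**2. What the bridge covers.** Section 1 uses group 1 to rule out an effect of the change to the HepB-containing vaccine. It is not aimed at differences between the children of group 2 and those of PIM.

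**3. The plan's own sample size.** Inputs from Section 4.4: variance of log10 GMC 0.27, difference 0.30, two-sided 5%, power 80%.

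- n = 2 × (1.960 + 0.842)² × 0.27 / 0.30² = 47.09. The stated 47 reproduces.
- 47 / 0.80 = 58.75, so 59 with 20% dropout. This reproduces too.

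The formula has no term for bias, so it describes an unconfounded comparison.

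**4. What an assumed bias would do.** Take 53 per group (66 × 0.80 = 52.8). For PIM this number is itself an assumption.

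- SE = √(0.27 × 2/53) = 0.101.
- Bias b = imbalance × log10(fold effect of the covariate).
- Error = P(|Z + b/SE| > 1.96) with no true vaccine effect.

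| Assumed imbalance and effect on IgG | b | Spurious GMC ratio | Error per serotype |
|---|---|---|---|
| 20 points, 1.5-fold | 0.2 × 0.176 = 0.035 | 1.08 | about 6.4% |
| 30 points, 2-fold | 0.3 × 0.301 = 0.090 | 1.23 | about 14.5% |

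Other assumed spurious ratios of 1.1, 1.2 and 1.3 give 6.9%, 12.3% and 20.4%. The variance 0.27 belongs to 6B, the serotype with the highest variance. For less variable serotypes the same bias would weigh more.

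**5. The same bias in the other direction.** With a true 2-fold difference, power at 53 per group is 84%. If the assumed bias of 0.090 offsets it, (0.30 − 0.090)/0.101 − 1.96 ≈ 0.12, and power falls to about 55%.

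**6. What adjustment costs or gains.** If covariates explain 5-20% of the outcome variance (assumed), the required n falls from 48 (47.09 rounded up) to 45-38 per group. If they explain 10-20% of group membership and nothing of the outcome (assumed), n rises to 47.09/0.9 = 53 or 47.09/0.8 = 59, against about 53 evaluable. For B cells, 33 × 0.90 × 0.85 = 25.2 evaluable per sub group, which leaves room for few covariates.

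**The case against.** The protocol does not hide the design. Section 3 says that randomisation is within each group and why, and Section 9.1 will show baseline comparability, naming day care. So a reader who infers that the protocol presents the vaccine comparison as randomised goes further than the text: the label is loose, and the same section corrects it. Disclosure does not remove the bias, however, and a baseline table does not adjust for anything.

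Other stronger readings also lack support:

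- **That the powered IgG test compares groups 1 and 2.** It compares group 2 with PIM. Recruitment differences between groups 1 and 2 bear on the cellular outcome.
- **That natural boosting confounds every serotype.** Section 1 says that the seven PCV7 serotypes are not under its influence. Among the ten serotypes common to both vaccines, this argument concerns the three that PCV10 adds. Other confounders could still affect the rest.
- **That group 1 had 5% uptake.** This was an expectation for all groups; only the 2% in group 2 is an observed rate.
- **That season clearly separates groups 1 and 2.** The invitation dates put the first births only about one to two months apart, although enrolment in group 2 runs for 3.5 months.
- **That every covariate is at hand.** Section 7.1.3 covers this study only. The protocol does not show what PIM recorded, and Table 1 places the questionnaire around the 11-month visits, so its values are not baseline values.

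The assumed biases are also well below the 2- to 2.5-fold difference that Section 4.4 regards as real. That stands as a limit on how serious they are. But the test is against a ratio of 1, and an observed ratio of about 1.58 (10^(1.96 × 0.101)) would already be significant at 53 per group. A 1.23-fold bias supplies 0.090/0.198 = 45% of that on the log scale.

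**Conclusion.** The point holds, and it concerns the analysis and the label, not the sample size, which reproduces. Vaccine is not randomised in either primary contrast, the named tests are unadjusted, the protocol limits the covariates to exploration, and the bridge through group 1 does not deal with participant differences.

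The documents give neither the size nor the direction of the bias. The range of about 6% to 15% error per serotype rests on assumed spurious ratios of 1.08 to 1.23, variance 0.27 and 53 evaluable on each side. A reader might infer that the error rate is known to be inflated, or that several factors must add up. Neither follows, since biases may also cancel. What can be said is that the plan has no pre-specified analysis that would reveal or reduce such a bias, and that one is cheap to add. It should be changed; it does not invalidate the trial.

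**What to change.** - **IgG, group 2 against PIM (9.1-9.3).** Pre-specify a linear regression of log IgG on vaccine group with a short fixed list, for example sex, day care, siblings, breast feeding, and age or interval since last dose at sampling. Use only covariates that PIM also holds, and check this before fixing the list. Show the unadjusted GMC ratio beside the adjusted one.
- **IgG, group 1 against group 2 at 12 months.** Add the same regression. Table 1 schedules this sample in all four sub groups, and the comparison is free of the study difference with PIM.
- **B cells.** Keep Mann-Whitney and add an adjusted log-scale or rank-based analysis as support, with few covariates given about 25 evaluable per sub group.
- **Choice of covariates.** Leave ear infections and recent antibiotic use out of the main list. They are recorded at about 11 months and could be consequences of the vaccine. Dates of vaccination and sampling are not in the Section 7.1.3 list and should be added to it.
- **Wording.** In the Summary and Section 3, describe a non-randomised vaccine comparison with randomised sampling time. State calendar period and unmeasured selection as limitations, since adjustment cannot remove them.

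The cost is some analysis work, a few degrees of freedom, and some loss of precision if the covariates predict group but not outcome. No more children or visits are needed.
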